### Data collection

#### Baseline data

Data collected at baseline by the call centre, prior to randomisation includes: demographic data, information on previous use of weight loss programmes including commercial services, current physical activity levels (using the International Physical Activity Questionnaire-short form (IPAQ-short)) [24] and use of weight loss medication. Patients allocated to the choice arm are asked about their reasons for choosing their programme.

When participants attend their first weight-loss session in the six interventions, the leader/counsellor measures participants' height and weight. Scales are validated by the research team using standardised weights, unless evidence of recent independent validation is provided. The commercial providers often use self-reported height, so this will be re-measured at follow-up by the blinded assessor. People in the comparator control group and people who are randomised but who do not attend their allocated programme are contacted and a researcher makes an appointment to measure height and weight.

During the 12-week programmes the service providers record weights on each visit. The comparator group are weighed at baseline only.

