### Population

Eligible participants are registered with general practices in South Birmingham Primary Care Trust, aged ≥ 18 years, with a raised BMI recorded within their primary care notes within the previous 15 months. The BMI threshold for invitation is that which makes them eligible for primary care obesity management services within the NHS and varies according to ethnic group and the presence or absence of co-morbidities. The threshold for invitation for people with no obesity-related comorbidity is a BMI of ≥ 30 Kg/m^2 ^in any ethnic group except South Asian and BMI ≥25 Kg/m^2 ^in South Asians. For people with obesity related comorbidity the threshold for invitation is a BMI ≥ 28 Kg/m^2 ^for all ethnicities apart from South Asians, for whom it is BMI ≥ 23 Kg/m^2^.

Their GP has to confirm that they have no medical contra-indications for any of the intervention programmes. Patients are excluded if they are unable to understand English, are pregnant or are unwilling to be randomised.

Recruitment commenced in January 2009. Each general practice identifies eligible patients using a search of the computerised clinical record and invites them by standard letter to participate in the weight loss trial. Practices are asked to exclude patients with serious co-morbidities for whom weight loss programmes were unfeasible or inappropriate, for example those with terminal illness. The invitation letter contains information about the trial and a toll-free telephone number for a call centre managing the recruitment and randomisation. The nurses at the call centre provide more information to patients about the trial, answer questions, collect baseline information, take verbal consent and randomise patients to the trial arms. The call centre books participants into their first treatment session and sends confirmation, along with verification of consent and information on how to withdraw from the trial if they change their minds. Participants allocated to the general practice, pharmacy or minimal exercise intervention (comparator) arms are sent details about how to arrange their first session.

The randomisation sequence was prepared by an independent statistician and to ensure blinding, each allocation was placed in an opaque, consecutively numbered envelope. These are used in order by the call centre staff, who record the number of the envelope and time of randomisation to enable the study team to check these are used in the correct order.

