### Planned analysis

Both between and within group analyses for primary and secondary outcomes at programme end and 12 months will be performed according to intention to treat. Participants in whom weight at follow up is not available will be assumed to have their baseline weight. However, sensitivity analysis will also be undertaken, assuming follow up weight to be the last recorded weight.

As the outcomes are all measured on a continuous scale (weight loss, percentage weight loss, self-reported physical activity), differences between intervention group and the comparison (minimal intervention) group will be investigated using least squares linear regression. Between group analyses will be expressed as both unadjusted and adjusted differences (corrected for baseline score and covariates of age, gender, ethnicity and educational level). A secondary analysis will compare the outcomes of the commercial weight loss programmes (Weight Watchers, Slimming World and Rosemary Conley) with the primary care programmes (general practice and pharmacy-based interventions). Data on choice of programme, number of sessions attended and reasons for drop-out will be presented using descriptive statistics.

To determine whether the service reaches those most in need, the age, gender, and deprivation score (derived from the postcode of residence) of those who were randomised will be compared to those who received the letter but did not respond or declined to be randomised.

Responses to open-ended questions about experience of the service and reasons for dropping out of their allocated programme will be categorised and presented descriptively.

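### The baseline weight that defines the primary outcome is measured after allocation, by routes and at times that depend on the arm, and no pre-randomisation weight is listed as a fallback

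*Protocol article*

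**What the plan says.** All references are to the Protocol article.

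- **Before randomisation.** Under Baseline data: "Data collected at baseline by the call centre, prior to randomisation includes: demographic data, information on previous use of weight loss programmes". The list goes on to physical activity and weight loss medication. Weight is not on it.
- **After randomisation, people who attend.** Same section: "When participants attend their first weight-loss session in the six interventions, the leader/counsellor measures participants' height and weight".
- **After randomisation, everyone else.** One sentence covers both the comparator arm and non-attenders; of the latter it says: "people who are randomised but who do not attend their allocated programme are contacted and a researcher makes an appointment to measure height and weight". The article gives no window for this appointment and does not say what happens if it is refused.
- **When the first session happens.** Under Population: "The call centre books participants into their first treatment session and sends confirmation". But also: "Participants allocated to the general practice, pharmacy or minimal exercise intervention (comparator) arms are sent details about how to arrange their first session". Interventions and Table 1 add that the commercial programmes run continuously without a fixed start, while a Size Down group is closed and starts together.
- **Analysis.** Under Planned analysis, a missing follow-up weight is replaced by the baseline weight, with the last recorded weight as a sensitivity analysis. Differences are given unadjusted and adjusted, the latter "corrected for baseline score and covariates of age, gender, ethnicity and educational level". The stated principle is intention to treat.
- **What exists before allocation.** Eligible patients are those "with a raised BMI recorded within their primary care notes within the previous 15 months".

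**The concern.** Weight loss is follow-up weight minus starting weight, so the starting weight is half of the primary outcome. Randomisation protects a baseline only if it is recorded before allocation can affect it. Here participants learn their arm first, then wait a time that depends on the arm, and are then weighed. Those who attend a programme are weighed by its leader or counsellor, who knows which programme it is. If people begin to diet, or eat more freely, while they wait, that change falls outside the measured interval, and may do so to a different extent in each arm.

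The second problem is a starting weight that is never obtained. The people at risk are those who do not attend and also decline the researcher's appointment. Their number probably varies between arms with a pre-booked session and arms in which the participant must arrange one. The trial compares programmes to inform commissioning, so a bias that depends on uptake would act on the comparison that matters.

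**Working it through.** **1. The plan's own figure.** Inputs from Sample size: difference 2 kg, SD 3.2 kg, 90% power, 5% significance (taken as two-sided), 20% dropout.

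n = 2 × (1.96 + 1.28)² × 3.2² / 2² ≈ 54 per group; 54 / 0.8 = 67.5, so 68. A t-test calculation gives 55, then 69. Both agree with the stated 70. The total is 6 × 100 + 2 × 70 = 740, as stated. No stated figure is in dispute.

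**2. Where each arm's starting weight comes from.**

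| Arm | Measured by | Timing after allocation |
|---|---|---|
| Three commercial programmes | group leader | pre-booked session, rolling start |
| Size Down | group leader | pre-booked, next closed group |
| General practice, pharmacy | counsellor | participant arranges the visit |
| Choice | as for the chosen programme | as for the chosen programme |
| Comparator | researcher | appointment, no window stated |
| Non-attenders, any programme | researcher | appointment, no window stated |

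Every route comes after allocation, and timing differs in kind between arms. The article does not give the length of any delay.

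**3. How sensitive the result is to a shift before weighing.** The documents give no shift, so a range is assumed. With 100 per arm, SE = 3.2 × √(2/100) = 0.4525 kg. With no true effect and a between-arm shift s, the false-positive rate is 1 − Φ(1.96 − s/SE) + Φ(−1.96 − s/SE).

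| Assumed shift s | Share of 2 kg | False-positive rate (nominal 5%) |
|---|---|---|
| 0.25 kg | 12.5% | 8.6% |
| 0.5 kg | 25% | 19.7% |
| 1.0 kg | 50% | 59.9% |

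**4. What a missing starting weight does.** There are two cases.

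- *No starting weight and no follow-up weight.* The carry-forward rule calls for a baseline weight that does not exist. The last-recorded-weight analysis has nothing earlier to use.
- *No starting weight, but a self-reported weight at three months*, which Outcome assessment allows. Follow-up is available, so the carry-forward rule does not apply, yet change cannot be computed.

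In both cases the regression that corrects for baseline lacks its covariate.

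**5. Size, if such people are lost.** The missing rate is also assumed. Suppose a fraction f of an active arm is lost, those lost gain nothing over the comparator, the comparator loses nobody selectively, and the true difference among all randomised is 2 kg. The estimate becomes 2 / (1 − f).

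| f | Estimated difference |
|---|---|
| 5% | 2.11 kg |
| 10% | 2.22 kg |
| 20% | 2.50 kg |
| 30% | 2.86 kg |

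**6. Power.** With everyone kept, power for 2 kg is 99.3% (100 v 100) and 98.0% (100 v 70). With 30% of the active arm lost it is still 98.0% and 94.8%. The issue is bias, not power.

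**The case against.** **A baseline at programme start is defensible.** The three-month assessment is timed from programme start, so starting the weight at the same point measures the programme and not the wait. This stands as a reason to keep the measured weight as the main baseline. It does not make that weight independent of allocation.

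**The plan works to limit loss.** The call centre telephones after the first session and rebooks, non-attenders are contacted and offered measurement, and scales are validated. This stands too: it reduces missing baselines and differences between scales. It does not cover refusal, and it does not address timing.

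**A record value used only where measurement failed creates its own imbalance:** attenders get a current weight and non-attenders possibly an old one. That is fair, and is why a sensitivity analysis using the pre-randomisation value for everyone belongs in the fix. It is also true that if follow-up is missing as well, carrying the fallback forward gives zero change whatever the value.

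**Stronger readings that the article does not support.**

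- A reader might infer that the adjusted analysis drops never-attenders while the unadjusted one keeps them at zero, so that the two use different populations. The article says neither. Read literally, the rules give both analyses no value; read as intention to treat, both could score zero. Handling of a missing baseline may be set out in the analysis plan, which is not shown.
- A reader might assume that attenders lose 4 kg and that 10–15% of the arm has no baseline, and compare an arm mean of 4.0 kg (dropped) with 3.6 or 3.4 kg (scored zero). That 0.4–0.6 kg is a shift in one arm, not in the contrast. With the same loss in a comparator losing 2 kg, the contrast moves only from 2.0 to 1.8 or 1.7 kg.
- A reader might take it that every participant's notes hold a weight. Only a BMI up to 15 months old is required. A weight behind it is likely, since practices were contracted to record height and weight (Background), but this is not stated for each person.
- Nor does the article show that the researcher's appointment falls later than first sessions, or that the call centre collects no weight at all. It gives no timing, and its list of call data may be condensed.

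**Conclusion.** The concern holds in this form: the weight that anchors the primary outcome is taken after allocation, by people and at times that depend on the arm. The article states no window for the researcher's appointment and no fallback if it fails. This is a matter of data collection, so an analysis plan could not supply an allocation-independent starting weight that nobody had collected.

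The size is unknown. The documents give neither the delays nor the share of missing baselines. On assumption only, a 0.5 kg between-arm shift would be a quarter of the target difference and raise the false-positive rate from 5% to about 20%. A 10% selective loss from an active arm would turn 2.0 kg into about 2.2 kg. Losses in the comparator could make the second figure smaller. These figures show that modest disturbances would matter; they do not show that any occurred. The change is worth making because it costs little.

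**What to change.** 1. Ask for current self-reported weight in the existing pre-randomisation call, for participants still to be recruited. Recruitment began in January 2009, so this cannot reach those already randomised.
2. For all participants, extract from the practice record the weight, or the BMI with height, and the date behind the qualifying BMI. This can be done retrospectively.
3. Keep the measured weight as the main baseline. Where it is missing, use the pre-randomisation value, with the order of preference between self-report and record fixed in advance, so that all randomised participants stay in both the unadjusted and adjusted analyses.
4. Add a sensitivity analysis of follow-up weight adjusted for the pre-randomisation weight in every participant, in place of the post-allocation baseline.
5. State a window for the researcher's appointment, and record the date of every baseline weighing so that the interval from allocation can be reported by arm.

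The cost is one question in a call already made and one extraction from records already searched. The downside is noise: the record value may be up to 15 months old, and self-report is less exact than measurement. Because both precede allocation, their errors cannot depend on the arm. As a covariate they cost precision; as a fallback starting weight for non-attenders they are weaker, and the number of participants who rely on them should be reported by arm.

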#### Outcome assessment

The primary outcome is weight loss at three months follow-up. The secondary outcomes are self-reported physical activity using the IPAQ-Short version, weight loss at one year and percentage weight loss at 3 months and one year.

At three months after programme start (programme end) the service providers weigh participants. Participants who are no longer attending their allocated programme are contacted and offered follow-up at home or another convenient location. If participants decline to be followed-up in person, they are asked to provide a self-reported weight, which is recorded as self-report. In addition, the IPAQ-short is administered by phone and participants who have dropped out of their allocated programme are sent an open-ended question asking for their views about the weight loss programme to which they were allocated.

The final outcome assessment takes place one year after randomisation. In addition to assessment of their BMI, participants are asked to complete the IPAQ-Short, their opinion of the service and whether they have tried any other weight loss programmes or strategies over the course of the year. Participants are invited to attend their general practice for a brief appointment, where the practice nurse or a health trainer who is blind to the allocation arm, undertake follow up measures. Participants unable to attend their general practice will be offered home visits for measurements. If height has not been measured previously, it is assessed using a Leicester height measure. Participant flow through the trial is shown in figure 1.

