This research protocol was developed in response to a need for South Birmingham Primary Care Trust (PCT) to develop services for the management of obesity. The PCT had identified that there were insufficient weight management services available in the National Health Service (NHS) and wished to develop these. As part of this, general practitioners (GPs) had been contracted to record height and weight of their patients. One option was for GP practices or NHS pharmacies to provide weight management services, for which the PCT would reimburse these practitioners. However, in the UK, there are many well established commercial companies that provide weight management services that are widely recognised and commonly used by those seeking help to lose weight. The PCT wished to contract with services that would have a high reach, good acceptability, and showed evidence of effectiveness and cost-effectiveness. Thus the aim of this trial was to determine the effectiveness of a range of NHS and commercial weight loss programmes in an unselected primary care population and to determine the characteristics of people responding to an unsolicited letter of invitation from their general practitioner.

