### Interventions

The content and delivery of the interventions are described in the Table 1. In addition the interventions have been classified according to Abraham and Michie's taxonomy of behaviour change techniques [19] by extracting the elements of the interventions from written manuals and materials provided by the programmes.

**Table 1 T1:** Characteristics of weight management programmes

	Weight Watchers	Slimming World	Rosemary Conley	NHS Size Down	General practice/pharmacy
Professional background of therapist	Successful group members selected through interview process. No formal qualifications required prior to training and selection.	Successful group members selected through interview process. No formal qualifications required prior to training and selection.	Varied, may be successful slimmers. No formal qualifications required prior to training and selection.	Food advisors recruited from local community. No formal qualifications required prior to training and selection.	GP: practice nurse or general practitioner Pharmacy: pharmacist

Training of therapist	4 visits to meetings to observe and deliver elements, admin workshop; 3 day residential workshop; Further 4 meetings delivering practical elements, one admin workshop.	4 day foundation training course; 4 advanced training courses.	OCR Exercise to music training. Certificate in applied nutrition and weight management. Business management and marketing. Attendance at annual training conferences and convention.	NVQ level 3, 12 × 2.5 hour training sessions from dieticians and nutritionists. 18 assessments.	2 day adult weight management course.

Assessment of therapist's competence	Assessed by area manager, who has observed all training sessions apart from 3-day workshop.	Completion of training course and 4 diploma exams. Observations at 1^st ^and 6^th ^sessions (minimum); twice yearly development visits by manager.	Theoretical papers and practical assessment by independent body. Assessed taking class once started. Annual business review.	Observed running session prior to passing the course.	Observed during the training course by leader e.g. Q&A, mock-interviewing.

Fidelity checking of intervention	Regular observations by area service manager. Buddy system during first year.	Weekly planning and training phone call with manager; regular observations of groups. Monitoring of retention to group, weight loss achieved.	Mystery shoppers used. Random checks.	Monthly supervision meetings.	None.

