The participants allocated to the commercial operators Weight Watchers [20], Slimming World [21] and Rosemary Conley [22] have a choice of programme locations and times. Commercially, these programmes run continuously, with no set number of sessions and no fixed starting date. People who are not participating in the trial pay fees to attend these programmes and these people attend alongside those in the trial, for whom treatment is free. Each programme is provided in accordance with the respective organisations' guidance and the group leaders are trained by the organisations. The vouchers provided to trial participants exempts them from payments for the first 12 weeks of the programme. Thereafter, if participants wish to continue attending sessions they are required to pay the appropriate fees to the service provider. The Size Down Programme is an NHS group-based programme in which all members of the group commence together and follow a prescribed course of sessions. It takes place in various community venues. Participants randomised to the general practice or pharmacy arms attend one-to-one sessions in the general practice or pharmacy. Appointments are made at a time mutually convenient to the participant and the nurse/pharmacist.

In the choice arm, participants are able to choose from any of the intervention programmes described above.

Participants allocated to the comparator group are sent vouchers for 12 free sessions to attend a local authority run leisure centre (typically including an exercise room, swimming pool, and other facilities such as squash or badminton courts). Participants are not given an appointment to attend and are given no dietary or individual physical activity advice and support. It is acknowledged that weight loss can occur with exercise-only, but effects are modest [8,23].

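### The primary 3-month weight is taken by the unblinded provider for programme attenders but by another route for everyone else, and the stated analysis does not examine measurement source

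*Protocol article*

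**What the plan says.** The protocol article, Outcome assessment, defines the endpoint: "The primary outcome is weight loss at three months follow-up". The same section then sets out three ways of obtaining that weight.

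- Attenders: "At three months after programme start (programme end) the service providers weigh participants".
- People who have stopped attending: "Participants who are no longer attending their allocated programme are contacted and offered follow-up at home or another convenient location". The person who weighs them is not named and is not said to be blind.
- People who decline to be seen: "If participants decline to be followed-up in person, they are asked to provide a self-reported weight, which is recorded as self-report".

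The comparator receives leisure-centre vouchers only. Interventions says of this group: "Participants are not given an appointment to attend and are given no dietary or individual physical activity advice and support". Under Baseline data, a researcher arranges its baseline weighing, and it has no weighings during the 12 weeks. Its 3-month assessor is not stated.

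A weigher blind to allocation is described only at one year, when weight loss is a secondary outcome. The other mention of a blinded assessor, in Baseline data ("this will be re-measured at follow-up by the blinded assessor"), concerns height.

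Planned analysis names the adjustment covariates (baseline score, age, gender, ethnicity, education). It carries the baseline weight forward when follow-up is missing, and gives one sensitivity analysis, which uses the last recorded weight instead.

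**The concern.** In each comparison of a programme with the comparator, the kind of person who records the primary outcome differs by arm and, within the programme arms, by attendance. Providers know the allocation because they deliver the programme, and some have a reason to want a good result. Table 1 lists, among Slimming World's fidelity checks, "Monitoring of retention to group, weight loss achieved". Background gives the commissioner's interest: "The PCT wished to contract with services that would have a high reach, good acceptability, and showed evidence of effectiveness and cost-effectiveness". This is a reason for care, not evidence of misconduct.

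If providers recorded 3-month weights more favourably than baseline weights, through rounding, clothing allowance or choice of reading, the error would add to the programme-comparator difference. A larger sample would not remove it. Neither the covariates nor the sensitivity analysis would reveal it. The last-recorded-weight analysis may even extend the asymmetry: in the programme arms the last weight is usually a provider's, whereas the comparator has only its baseline weight to fall back on.

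**Working it through.** **The plan's own figure.** Inputs from Sample size: difference 2 kg, SD 3.2 kg, 90% power, 5% significance (taken as two-sided), 20% dropout.

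n per group = 2 × (1.960 + 1.282)² × 3.2² / 2² = 53.8, so 54. Then 54 / 0.8 = 67.5, so 68, close to the stated 70. The total 6 × 100 + 2 × 70 = 740 agrees exactly. This point changes neither figure.

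**Which errors survive.** The outcome is change from baseline. Attenders' baseline weight is also taken by the provider, on scales validated by the research team or independently. A constant scale offset or a constant clothing practice therefore cancels. What remains is a change in practice between baseline and 3 months, or selective recording at 3 months.

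**Size, on assumed values.** The documents give neither the mean error b nor the share q of a programme arm weighed by the provider. I take b = 0.25, 0.5 and 1.0 kg and q = 50-100%, with no true effect.

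- Shift in the arm mean = b × q.
- SE of the difference = 3.2 × √(1/n₁ + 1/n₂). This is 0.453 kg for 100 v 100, and 0.499 kg for 100 v 70 (comparator against general practice or pharmacy).
- Rejection rate = Φ(shift/SE − 1.96) + Φ(−shift/SE − 1.96).

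Example, b = 0.5, q = 100%, 100 v 100: 0.5/0.453 = 1.105, so Φ(−0.855) + Φ(−3.065) = 0.196 + 0.001 = 19.7%.

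| Error b | Shift (q 50-100%) | Part of the 2 kg target | Rejection, 100 v 100 | Rejection, 100 v 70 |
|---|---|---|---|---|
| 0.25 kg | 0.125-0.25 kg | 6-12.5% | 5.9-8.6% | 5.7-7.9% |
| 0.5 kg | 0.25-0.5 kg | 12.5-25% | 8.6-19.7% | 7.9-17.1% |
| 1.0 kg | 0.5-1.0 kg | 25-50% | 19.7-59.9% | 17.1-51.8% |

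**What a shift analysis would show.** Holding the SE fixed, a result loses significance at a shift of about (estimate − 1.96 × SE) / q. With 100 v 100, 1.96 × 0.453 = 0.89 kg.

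- Observed difference 2 kg: (2 − 0.89)/q = 1.11 kg at q = 100% and 2.22 kg at q = 50%, so it survives the whole 0.25-1.0 kg range.
- Observed difference 1 kg: (1 − 0.89)/q = 0.11 to 0.22 kg, so it fails at the smallest shift.

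The risk therefore bears mainly on modest effects.

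**The case against.** The strongest defence is that weight is an objective measure, the choice of assessor is pragmatic and openly described, scales are validated, and the provider takes both weights, so much of the possible error cancels. The blind one-year weight is already to be analysed between groups, and self-reports are already flagged. An analysis by measurement source is the kind of detail a separate analysis plan may hold, and none is shown here.

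Much of this stands. The absence of such an analysis would not be a finding by itself. But the article itself fixes the primary-outcome assessor by arm and attendance, and the covariates and sensitivity analysis it does state leave that untouched. Validation controls the instrument, not the recording. The one-year weight is a partial check only, because it is secondary and about nine months later.

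Four stronger readings are tempting, but the documents do not support them:

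- *The comparator is weighed at home or another convenient place.* Outcome assessment gives that route only for people no longer attending a programme. That the comparator lies outside the provider route is an inference from its having no provider. The remark that it is weighed at baseline only follows a sentence on weights during the 12 weeks, and need not mean that no 3-month weight is taken.
- *Error can act only in the programme arms.* Self-report error may arise in any arm and could offset the provider error.
- *Providers' contracts depend on the result.* Background states what the commissioner wished for, not a condition. The weight-loss monitoring is listed for one provider, and fidelity checking in general practice and pharmacy is given as none.
- *Bias is present.* Nothing in the documents shows it.

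**Conclusion.** The point holds as a risk that the plan should address. Providers weigh attenders for the primary outcome, non-attenders take another route, the comparator has no provider, and blind weighing is reserved for a secondary time point. Every programme-comparator contrast at 3 months therefore mixes treatment effect with measurement source to an unknown extent. Comparisons among provider-weighed programmes are less exposed.

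The size rests on assumption. Over the ranges shown, the consequence runs from negligible (about 6% false positives) to severe (about 60%), and the net direction cannot be found from the documents. That uncertainty is the reason to report a tipping point rather than one corrected estimate.

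**What to change.** Keep the weighing arrangements and make four changes.

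1. For every 3-month weight, including the comparator's, record who took it: provider, researcher or self-report.
2. Add a sensitivity analysis that reduces provider-recorded 3-month losses by amounts from 0.25 to 1.0 kg, leaves other weights unchanged, and reports the shift at which each programme-comparator result loses significance.
3. Describe the 3-month outcome as open and provider-assessed for attenders.
4. Present the blind-assessed one-year difference beside it.

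Do not turn this into a pass/fail rule for effectiveness at a fixed shift such as 0.5 kg: nothing in the documents calibrates such a threshold.

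The cost is one recorded field, a short extra analysis and some wording, with no new visit, assessor or participants. The price is a somewhat more cautious 3-month conclusion.
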